### Participants and sampling

All CHWs in each of the 20 eligible PCUs located in São José dos Campos will be invited to take part. Individuals working as a CHWs for less than 3 months will be excluded. Each PCU has approximately from 8 to 12 CHWs, totalling 160 to 240 potential participants. A proportion (30%) of refusals to participate and dropouts are expected (eg, change in work schedules); therefore, we estimate to include approximately 14 PCUs involving around 150 participants in the trial.

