#### Method of generating the allocation sequence

Randomisation and allocation will be conducted by blinded member of the research team at the PCU level using computer-generated random numbers. The PCUs whose managers agree to participate will be randomly allocated in two parallel groups—experimental group or control group—so that all CHWs of a given PCU who voluntarily accept to take part can be allocated in the same group forming a cluster and reducing the potential for contamination (eg, sharing knowledge learnt in the intervention between PCUs). The allocation will be made randomly at 1:1, so that there is the same number of PCUs in each group, offering as much as possible balanced participation among CHWs from PCUs located in the various geographical regions, proportional to the total number of PCUs of each region (20%: north, 20%: south, 20%: east, 20%: west, 20%: centre). The characteristics of participants (eg, age, gender, time working as CHW) will be compared between groups and controlled statistically if significant differences are observed.

Before informing the PCUs about the group to which their CHWs have been allocated, every CHWs wishing to participate will read and sign a consent form. Recruitment and enrolment will be conducted by a separate member of the team, who will be blinded to the allocation. Then, all participants will be invited to complete the baseline measures (t1). The experimental group will be informed about the dates and timings of the intervention and the control group will be told that they will be allocated to a waiting list. After the completion of the final assessments from both experimental group and control group (t2), the intervention will be offered to the control group.

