#### Data analysis

We will seek to adhere to the steps proposed in the modelling phase of the Medical Research Council guidelines for developing complex interventions.^42^ The purpose of a feasibility study is not to make a formal analysis of the primary outcome, but to evaluate trial processes to determine whether to progress to a study of effectiveness and to estimate parameters needed to design the future trial.^42^ Data analysis will be conducted by a researcher who has not been involved with the intervention itself and who is blinded to the arm allocation. Double data entry and checking will be used to ensure accuracy.

We hypothesise that the intervention is feasible and might be able to improve knowledge, attitudes and intended behaviour in relation to dementia among CHWs. Analysis of quantitative data will be based on ‘intention to treat’, that is, data from all participants will be included regardless of their withdrawal from the study or not. Descriptive analysis will include central and dispersion measures, according to the types (eg, continuous, categorical, nominal) and distribution patterns of the variables, including number of incomplete responses and dropouts, ceiling and floor effects. Differences in levels of variables related to dementia stigma, namely, knowledge, attitudes and intended behaviours towards people living with dementia, before and after the intervention, between groups and between time points (t0 and t2), will be analysed using Student’s t test or a non-parametric test, according to data distribution. We will measure internal reliability (Cronbach’s alpha) and test–retest, levels of variance, correlation between sociodemographic variables and between the different outcome variables. An appropriate statistical approach will be chosen to handle any missing data depending on its pattern and type of variables.

Quantitative feasibility measures will be analysed descriptively and will be compared with the results from the outcome measures. Feasibility data collected through qualitative methods will be analysed in an integrated manner using content analysis as well as triangulation techniques in NVivo.^43 44^ In preparation to that, semistructured interviews will first be transcribed anonymously and verbatim.

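### Primary care units are randomised as clusters, but the secondary stigma outcomes are to be compared with tests that make no allowance for the unit

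*Protocol article*

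**What the plan says.** **Design.** In the section on generating the allocation sequence, allocation is made at PCU level by computer-generated random numbers. All consenting CHWs of one PCU "can be allocated in the same group forming a cluster and reducing the potential for contamination". Allocation is 1:1, with an equal number of PCUs per arm. Under Participants and sampling: "we estimate to include approximately 14 PCUs involving around 150 participants in the trial". Under Active intervention and control, the sessions are run separately for the CHWs of each experimental PCU, as a group.

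**Analysis.** The Data analysis section takes data from all participants under intention to treat. Differences in knowledge, attitudes and intended behaviour, between groups and between t0 and t2, "will be analysed using Student’s t test or a non-parametric test, according to data distribution". The article mentions no PCU summary, random effect, robust standard error or design effect.

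**Purpose.** The same section says that a feasibility study serves, among other things, to "estimate parameters needed to design the future trial". It lists internal reliability, test–retest, variance (without saying at which level) and correlations. It does not name an ICC.

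**The concern.** The two-sample t test and its rank-based alternative, applied to CHWs, assume that each CHW contributes independent information. The design gives two reasons to doubt this. CHWs in one PCU share a workplace and a community, and in the experimental arm they also share the same group sessions. Choosing between a parametric and a non-parametric test by the shape of the data does not help, because the fault is dependence and not non-normality. The t0 to t2 comparison is exposed in the same way wherever changes are correlated within a PCU.

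At stake is the apparent precision of the stigma results. Chance differences between seven PCUs and seven others would look more convincing than they are. Over-optimistic precision could also carry into the planning of a later trial.

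**Working it through.** **1. The plan's own size.** There is no power calculation to reproduce, only an expected size. With 20 eligible PCUs and 30% loss, 20 × 0.70 = 14 PCUs, which matches. With 8 to 12 CHWs per PCU, 14 × 8 = 112 to 14 × 12 = 168 CHWs. The stated figure of around 150 lies inside that range (midpoint 140) and is used below. 1:1 allocation gives 7 v 7 PCUs, with mean cluster size m = 150/14 = 10.71.

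**2. Assumptions not in the article.** ICC of 0.02, 0.05 or 0.10; a two-sided 5% level.

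**3. Formulas.**
- Design effect: DE = 1 + (m − 1) × ICC = 1 + 9.71 × ICC
- Effective sample size: 150/DE
- Approximate type I error of a test that ignores PCU: 2 × [1 − Φ(1.96/√DE)]

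| ICC | DE | √DE | Effective N | Type I error, formula | Type I error, simulated |
|---|---|---|---|---|---|
| 0 | 1.00 | 1.00 | 150 | 5.0% | 5.1% |
| 0.02 | 1.19 | 1.09 | 126 | 7.3% | 7.3% |
| 0.05 | 1.49 | 1.22 | 101 | 10.8% | 10.8% |
| 0.10 | 1.97 | 1.40 | 76 | 16.3% | 16.1% |

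The simulation used 20,000 null trials per ICC, 7 v 7 PCUs of 10 or 11 CHWs and normal outcomes, comparing the arms with an ordinary t test on CHWs. A second simulation with PCU sizes of 9 to 12 (8,000 replicates) gave 7.8%, 11.0% and 16.1% for the three non-zero ICCs. In the first simulation, a t test on the 14 PCU means (12 df) stayed at 4.9% to 5.2% for the ICCs in the table.

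**4. Interval width, in units of the total SD.** The standard error ignoring PCU is √(4/150) = 0.163.
- Ignoring PCU, 148 df: 1.976 × 0.163 = 0.32
- PCU means, 12 df, ICC 0.05: 2.179 × 0.163 × 1.22 = 0.43, a ratio of 0.434/0.323 = 1.34
- PCU means, 12 df, ICC 0.10: 2.179 × 0.163 × 1.40 = 0.50, a ratio of 0.500/0.323 = 1.55

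The ratio exceeds √DE because the critical value also rises, from 1.976 to 2.179.

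**5. How well this trial could estimate an ICC.** One-way ANOVA F method with 14 PCUs (13 and 136 df): at an estimated ICC of 0.05, F = 1.486/0.95 = 1.56, and the 95% interval is about −0.02 to 0.23.

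**The case against.** The strongest reply is that little in this trial depends on these tests. Feasibility is the primary outcome and the stigma measures are secondary. The Data analysis section says that a feasibility study does not aim at a formal analysis of the primary outcome, and the strengths and limitations list rules out conclusions on effectiveness. The progression rules (at least 70% completing two-thirds of sessions, less than 15% missing outcome data, fidelity of at least 75%) use no t test. All of this stands, and it limits the severity. It does not make the named test suit the design.

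A second reply is that a fuller protocol or analysis plan may deal with clustering. For the test this does not succeed: the article names a method, and that method does not match the randomisation. For the ICC the reply has force, because that part rests on silence.

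A reader might infer more than the text supports:
- **That no ICC will be produced.** The article only names none. Its reference to variance is unspecific and could cover the between-PCU component.
- **That a later cluster trial could not be sized.** It needs an ICC assumption, but not necessarily from this study, and 14 PCUs would give only an imprecise one. Nor does the article say that the later trial will be sized from the individual SD alone.
- **That the plan commits to misleading p-values and confidence intervals.** It mentions neither, and states no test level. Individual-level testing is the natural reading of a t test on all participants, and overstated precision follows only if the ICC is above zero.

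**Conclusion.** The mismatch is real and lies in the article's current text: clusters are randomised, and the test named for the secondary stigma outcomes makes no allowance for them. Its size depends on an ICC that the article does not give. Over the assumed range of 0.02 to 0.10, the nominal 5% becomes about 7–8% to 16%, and 150 CHWs carry the information of about 126 to 76 independent ones. At an ICC of zero there is no inflation. The figures are for a between-arm comparison of normal outcomes. The article also plans t0 to t2 comparisons and uses Likert-format measures, for which the direction is the same where responses or changes correlate within PCU, but the size was not computed.

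This should be fixed before analysis. It does not call the feasibility conclusions into question.

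**What to change.** Replace the sentence on the t test or non-parametric test with one of two analyses:
- a comparison of PCU means (12 df with 14 PCUs); or
- a linear mixed model with a random intercept for PCU and a small-sample degrees-of-freedom correction such as Kenward–Roger.

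Either should cover both the between-group difference and the change from t0 to t2. Report estimates with 95% confidence intervals and make no efficacy claim.

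Since estimating design parameters is a stated aim, add the ICC of each stigma domain with its confidence interval to the listed quantities. Say that it will be imprecise with 14 PCUs.

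The cost is analysis wording only, with no new data or participants. The visible price is honest width: the 95% half-width rises from 0.32 SD to 0.43 SD at ICC 0.05 and 0.50 SD at ICC 0.10, about 1.35 and 1.55 times.

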### Ethics and dissemination

This study was approved by the National Commission for Ethics in Research in Brazil (CONEP) (*n. 5.510.113*). Every individual taking part will be informed about their rights as participants, including the fact that non-participation will not affect in any way their work status or care received at the PCU. Every participant will sign a consent form; those participating in the semistructured interviews will be required to sign a second consent form specific for this research activity.

Safety monitoring procedures have been created to protect participants and researchers, including safety measures to prevent emotional impact and the spread of COVID-19 (eg, mandatory vaccination and use of mask during any study activity as well as physical distance during the study. All personal information about potential and enrolled participants will be collected, shared and maintained in line with the norms and regulations of the Brazilian National Ethics Committee (http://www.conselho.saude.gov.br/comissoes-cns/conep) regarding confidentiality measures stated in order to protect confidentiality before, during and after the study. Any important protocol modifications will be immediately communicated to the Research Ethics Committee and the study will be stopped until an approval is obtained for the study to continue. The study will not have a data monitoring committee as this is not required for a feasibility non-pharmacological study in Brazil.

We plan to disseminate this study in open-access scientific and community events related to dementia. The intervention materials will be published online and will be available for use by anyone who wishes to translate, adapt and implement it. Our research team works closely with policymakers as part of a national advisory team, which we hope will help increase the possibility of such intervention to be applied in more settings in Brazil. An antistigma intervention toolkit will be informed by this study will be accessible nationally in Brazil and globally through open-access publication to support researchers and practitioners with the implementation of dementia-related antistigma actions.

### Patient and public involvement

Through a series of focus groups and semistructured interviews, we have explored the views of family carers, people living with dementia, healthcare workers and members of the public about stigma and discrimination related to people living with dementia. The findings from this exploratory activity have informed the development of the intervention. We have also presented and discussed this intervention protocol among the international and multidisciplinary team (*Strenghtening Responses to Dementia in Developing Countries: STRiDE - www.stride-dementia.org*) for internal validation.^34^ As this is a protocol for a feasibility study, which involves both quantitative and qualitative procedures, we aim to gather participants’ views about the intervention as part of the study itself in order to improve it for a future trial. We will also continue to consult our international consortium, which includes experts by experience, about the various methodological and practical aspects of the work as it progresses.

### Planned study dates

We plan to start the study in August 2022 and to end it in January 2023.

## Discussion

The number of people living with dementia in Brazil is likely to increase in the next decades; however, the number of people who are undiagnosed remains high and there is limited access and availability of appropriate support. Improving knowledge, attitudes and behaviour of healthcare workers towards people living with dementia is a global health priority. In doing so, this is likely to reduce the stigma and discrimination experienced by people living with the condition, protect the quality of their lives, improve diagnosis rates and quality care. Antistigma interventions have been successful in other countries and disease contexts, such as other mental health conditions and HIV. However, there is a paucity of research on antistigma interventions related to dementia, particularly targeting healthcare workers.

To our knowledge, this is the first antistigma intervention related to dementia to be conducted in Brazil and we are not aware of any other similar intervention in other Latin American countries. We will target CHWs who are the first point of healthcare access for people living with dementia in the community and we hope that this will help increase the number of people living with dementia who are identified and attended by the healthcare systems. As CHWs work alongside multidisciplinary teams, we hope that the learning experiences achieved through this intervention will be shared among other members of the team, contributing to a further reach of the intervention and higher impact. The measures of feasibility included in this protocol will be paramount to ensure that the invention is acceptable, relevant and effective to be applied in a future randomised controlled trial in Brazil and in other LMICs. An antistigma toolkit will be created from the intervention will also help ensure fidelity of future trials as well as applicability in PCUs whose teams have the opportunity to apply it in their territories.
